# TremelImumab and Durvalumab Combination for the Non-OperatIve Management (NOM) of Microsatellite InstabiliTY (MSI)-High Resectable Gastric or Gastroesophageal Junction Cancer: The Multicentre, Single-Arm, Multi-Cohort, Phase II INFINITY Study

**DOI:** 10.3390/cancers13112839

**Published:** 2021-06-07

**Keywords:** gastric cancer, microsatellite instability, pre-operative treatment, PD-L1, CTLA4, non-operative management

## Abstract

**Simple Summary:**

The status of microsatellite instability (MSI-H) in gastric or gastroesophageal junction cancer (GC/GEJC) patients eligible for radical surgery proved to be prognostic for an improved survival outcome and predictive for poor/no benefit from the combination of adjuvant/peri-operative chemotherapy. MSI-H tumors display a high sensitivity to immunotherapy and exploratory studies showed that a pre-operative treatment with immune-checkpoint inhibitors may achieve elevated rates of pathological complete responses. The ongoing proof-of-concept INFINITY study is aimed at investigating the role of the combo-immunotherapy durvalumab plus tremelimumab as a neoadjuvant or potentially definitive treatment (avoiding surgery in case of complete clinical response) for MSI-H resectable GC/GEJC patients.

**Abstract:**

In resectable gastric or gastroesophageal junction cancer (GC/GEJC), the powerful positive prognostic effect and the potential predictive value for a lack of benefit from the combination of adjuvant/peri-operative chemotherapy for the MSI-high status was demonstrated. Given the high sensitivity of MSI-high tumors for immunotherapy, exploratory trials showed that combination immunotherapy induces a high rate of complete pathological response (pCR), potentially achieving cancer cure without surgery. INFINITY is an ongoing phase II, multicentre, single-arm, multi-cohort trial investigating the activity and safety of tremelimumab and durvalumab as neoadjuvant (Cohort 1) or potentially definitive (Cohort 2) treatment for MSI-high/dMMR/EBV-negative, resectable GC/GEJC. About 310 patients will be pre-screened, to enroll a total of 31 patients, 18 and 13 in Cohort 1 and 2, at 25 Italian Centres. The primary endpoint of Cohort 1 is rate of pCR (ypT0N0) and negative ctDNA after neoadjuvant immunotherapy, of Cohort 2 is 2-year complete response rate, defined as absence of macroscopic or microscopic residual disease (locally/regionally/distantly) at radiological examinations, tissue and liquid biopsy, during non-operative management without salvage gastrectomy. The ongoing INFINITY proof-of-concept study may provide evidence on immunotherapy and the potential omission of surgery in localized/locally advanced GC/GEJC patients selected for dMMR/MSI-high status eligible for radical resection.

## 1. Introduction

Gastric cancer (GC) and gastroesophageal junction cancer (GEJC) globally represent the fourth most common cancer and the second leading cause of cancer-related death [1]. Despite the evolution of the disease management thanks to the development of multimodality treatment strategies, GC/GEJC remains one of the most lethal malignancies with unsatisfactory long-term survival outcomes [2].

The cornerstone of potentially curative treatment remains surgery, specifically total/subtotal gastrectomy with lymphadenectomy. In the last decades, the research focused on the integration of systemic treatments for localized or locally advanced disease, in order to improve the survival outcome of patients and/or to increase the rate of radical surgical resections [3,4,5,6,7].

In detail, the MAGIC study first provided evidence that the combination of peri-operative chemotherapy with epirubicine, cisplatin and continuous fluorouracil (ECF) confers longer overall survival (OS) and a higher rate of curative resection than radical surgery alone [3]. Recently, the fluorouracil, oxaliplatin and docetaxel (FLOT) regimen showed improved survival outcomes as compared with ECF/ECX and is now considered the standard of care [4]. Otherwise, adjuvant chemotherapy in a GC setting was primarily supported by the ACTS-GC [6] and CLASSIC [5] studies, and the GASTRIC group meta-analysis [7]. Therefore, both chemotherapy approaches are now evidence-based and guideline-endorsed, the adjuvant schedule is preferred in Asian countries and the peri-operative one outside of Asia. Nevertheless, disease relapses still occur in a substantial number of patients, who eventually die for their disease and, on the other side, some patients are cured by surgery alone and do not require additional therapy, thus they receive potentially toxic treatments without a significant benefit [8,9].

The mismatch repair deficient (dMMR)/microsatellite instability high (MSI-H) status is widely recognized as a prognostic and predictive factor in colorectal cancer (CRC) [10,11]. Recently, in the setting of resectable GC/GEJC, the powerful positive prognostic effect for improved disease-free survival (DFS) and OS and the potential negative predictive value for a lack of benefit from the combination of adjuvant/peri-operative chemotherapy in MSI-H patients was shown [12]. Moreover, the importance of dMMR/MSI-H status emerged when it proved to represent one of the most powerful predictors of benefit from immunotherapy with anti-programmed death receptor 1 and its ligand (PD1/PD-L1) immune-checkpoint inhibitors (ICIs) so that pembrolizumab received the agnostic approval for adult and pediatric patients with advanced tumors bearing this alteration [13,14].

This evidence provided the rationale for the investigation of neoadjuvant immunotherapy in MSI-H tumors, aimed at maximizing the rate of disease eradication and the chance of cure for patients. The exploratory and proof-of-concept trials conducted so far, mainly in CRC patients, showed that the combination of anti-PD1/PD-L1 with anti-cytotoxic T-lymphocyte antigen 4 (CTLA4) agents is able to induce a very high rate of complete pathological responses (pCR) in patients selected for dMMR/MSI-H status, potentially achieving a curative power aside from surgery [15,16,17,18].

On this basis, the INFINITY study was designed, aimed at assessing the activity and safety of the combination of the anti-CTLA4 tremelimumab and the anti-PD-L1 durvalumab as a neoadjuvant or potentially definitive treatment for MSI-H, dMMR and EBV negative, early-stage and resectable GC/GEJC.

## 2. Materials and Methods

### 2.1. Study Design

INFINITY is a phase II, multicentre, single-arm, multi-cohort trial conducted in Italy. Patients affected by early-stage and resectable GC/GEJC selected for the presence of MSI-H, dMMR and EBV negative status centrally determined at the Co-ordinating Centre are eligible for the study.

Following the initial complete baseline disease staging, patients are administered a neoadjuvant treatment with combination immunotherapy composed of tremelimumab and durvalumab and, after the complete tumor restaging, they undergo the standard surgery according to the clinical practice and guidelines. Afterward, patients are followed in a standard follow up phase. After the completion of the enrollment in Cohort 1 and the extensive evaluation of the final results of Cohort 1 regarding all endpoints (including exploratory endpoints), and after potential amendment(s) on study design, eligibility criteria and study procedures requested by the Sponsor’s Steering Committee and an Independent Data Monitoring Committee made of foreign experts, and following the approval of the Ethics Committee and the Italian Medicines Agency, the enrollment in Cohort 2 will start. Patients enrolled in Cohort 2 will receive the same neoadjuvant treatment as in Cohort 1 and will be subjected to complete disease restaging; those with no evidence of complete clinical response will be subjected to standard surgery and subsequent follow up as in Cohort 1. Patients with complete clinical response will undergo a non-operative management (NOM), followed by standard follow-up in absence of disease recurrence/persistence, with salvage surgery in case of evidence of disease. The study design is depicted in Figure 1 and Figure 2.

### 2.2. Study Population

The study will be conducted in 25 Italian Cancer Centres and approximately 310 patients will be molecularly pre-screened, in order to enroll a total number of 31 patients, 18 in Cohort 1 and 13 in Cohort 2.

The main inclusion criteria are:written informed consent and any locally required authorizationage ≥18 years oldEastern Cooperative Oncology Group (ECOG) Performance Status (PS) 0–1body weight >30 kgdiagnosis of resectable GC or GEJC (Siewert II-III), categorized according to TNM classification 8th edition as cT ≥2, any cN, M0 or any cT, cN1-3, M0absence of distant metastases as defined by negativity of computed tomography (CT) and 18-fluorodeoxyglucose positron-emission tomography (18-FDG PET)MSI-H status confirmed by immunohistochemistry (IHC) and multiplex polymerase chain reaction (PCR) and EBV-negative status confirmed by means of silver in-situ hybridization (SISH for EBER), as determined centrally at the Co-ordinating Centre with lack of heterogeneity of dMMR status as showed by lack of tumor cells showing concomitant expression of all 4 protein markersadequate bone marrow and organ function.The main exclusion criteria account for:signs of distant metastasesprior medical treatments or irradiation for GC/GEJCmajor surgical procedure within 28 days prior to the first dose of treatmentprevious treatments with anti-CTLA4 or anti-PD1/PD-L1 ICIsallergy or severe hypersensitivity reaction to monoclonal antibodiesautoimmune diseases or history of organ transplantation that require immunosuppressive therapyactive primary immunodeficiencyactive infection including tuberculosis, hepatitis B, hepatitis Cuncontrolled intercurrent illness, or psychiatric illness/social situationswomen in pregnancy or lactation condition.

### 2.3. Study Endpoints

The primary objective of the study is to assess the activity of the combination immunotherapy with tremelimumab plus durvalumab as a neoadjuvant or definitive treatment of resectable MSI-H GC/GEJC. Therefore, the primary endpoint of Cohort 1 is the rate of pCR (ypT0N0) and negative ctDNA status after neoadjuvant immunotherapy in the intention-to-treat population. The primary endpoint of Cohort 2 is the 2-year complete response rate, defined as the absence of macroscopic or microscopic residual disease (locally, regionally and distantly) at radiological examinations, tissue and liquid biopsy, in absence of salvage gastrectomy.

Secondary endpoints are, for both Cohorts, 3-year DFS, defined as time from the enrollment in the study to the occurrence of disease relapse (local and/or distant), second GC/GEJC primary, or death from any cause; 5-year OS, defined as time from the enrollment in the study to the occurrence of death; metastases-free survival, defined as time from the enrollment in the study to the first evidence of metastases or death from any cause; the safety of the neoadjuvant combination immunotherapy, defined as the incidence of AEs during the treatment and follow-up phases, assessed according to common terminology criteria for adverse events (CTCAE v5.0), and its impact on patients’ quality of life, assessed thanks to patient reported outcomes (EORTC QLQ-C30, EORTC QLQ-STO22 and EuroQol EQ-5D, during pre-operative treatment phase). Additionally, for Cohort 2 the gastrectomy-free survival, defined as time from the inclusion in the study to the occurrence of gastrectomy or death from any cause, and for patients enrolled in Cohort 1 and for those enrolled in Cohort 2 and subjected to surgery, morbidity and mortality of gastrectomy following pre-operative tremelimumab and durvalumab.

Exploratory endpoints will involve translational analyses on tissue and blood biomarkers aimed at identifying which subgroup of patients may derive the highest chance of definitive cure from immunotherapy combination of tremelimumab plus durvalumab.

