The single-arm multi-cohort trial design is justified considering that, given the excellent 5-year DFS (70%) and OS (75%) of patients with radically resected MSI-H GC, clinical trials comparing a neoadjuvant/peri-operative immunotherapy approach with standard of care multimodality strategy (surgery +/− neoadjuvant chemotherapy) would require a very high number of patients to be enrolled to demonstrate a significant increase of survival above the outcomes historically achieved by surgical resection. The feasibility of such a trial is even impaired by the relatively low prevalence of MSI-H status in GC (about 9% in the recent meta-analysis [12]). Finally, even when hypothesizing positive and practice-changing results of such a trial, the majority of patients eligible for peri-operative immunotherapy would be overtreated since they are most likely cured with surgery alone. Therefore, given the significant morbidity and mortality of gastrectomy, and its potentially negative impact on long-term outcomes in terms of quality of life, there is a strong rationale for investigating PD-(L)1 plus CTLA4 blockade as a definitive treatment and NOM strategy in MSI-H GC in Cohort 2 based on the results of Cohort 1 of the INFINITY Study.

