**Monitoring**						
ECOG performance status		X	X	X	X	X
AE/SAE assessment		<----------------------------- All visits ----------------------------->				

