**Monitoring**			
ECOG performance status	X	X	X
AE/SAE assessment	X		
AE assessment		as clinically indicated	

**Table 3 cancers-13-02839-t003:** Schedule of assessments for Cohort 2 patients with clinical complete response.

Evaluation	Non-Operative Management (NOM) Strategy	
**Time from enrolment**	**Week 15–18**	
	**Phase 1: Protocol-scheduled follow-up Every 12 weeks for 2 years**	**Phase 2: Standard follow-up** **Every 6 months for 3 years**

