**Monitoring**		
ECOG performance status	X	X
AE assessment	as clinically indicated	

**Table 4 cancers-13-02839-t004:** Literature-based evidence on immunotherapy in MSI-H tumors.

Study	Disease Setting	Treatment	Results
KEYNOTE 059 [23]	Advanced previously treated GC	Pembrolizumab monotherapy	Overall response rate 11.6% overall trial population 57.1% MSI-H patients 9.0% MSS patients
KEYNOTE 061 [24]	Advanced GC progressing after platinum and fluoropyrimidine	Pembrolizumab vs. paclitaxel	*Overall population* Median OS 9.1 vs. 8.3 months (HR 0.82, 95% CI 0.66-1.03; *p* = 0.0421) Median PFS 1.5 vs. 4.1 months (HR 1.27, 95% CI 1.03-1.57)
			*MSI-H subgroup* Median OS not reached vs. 8.1 months (HR 0.42; 95% CI 0.13–1.31)
KEYNOTE 062 [25]	Advanced previously untreated GC	Pembrolizumab vs. chemotherapy	*Overall population* Median OS 10.6 vs. 11.1 months in CPS ≥1 (HR 0.91; 99.2% CI 0.69–1.18) while 17.4 vs. 10.8 months in CPS ≥10 (HR 0.69; 95% CI 0.49–0.97)
			*MSI-H subgroup* Median OS not reached vs. 8.5 months Median PFS 11.2 vs. 6.6 months
		Pembrolizumab plus chemotherapy vs. chemotherapy	Median OS 12.5 vs. 11.1 months in CPS ≥1 (HR 0.85; 95% CI 0.70–1.03; *p* = 0.05) while 12.3 vs. 10.8 months in CPS ≥10 (HR 0.85; 95% CI 0.62–1.17; *p* = 0.16)
Analysis of KEYNOTE-016, 164, 012, 028, 158 trials [13,26]	Mismatch repair deficient (dMMR) colorectal cancers (CRCs), dMMR non-CRC cancers, pMMR CRCs	Pembrolizumab	Objective response rate 62% in dMMR CRC 60% in dMMR non-CRC cancers 0% in pMMR CRCs
CheckMate 142 [27]	Metastatic previously untreated MSI-H CRC	Nivolumab plus low dose ipilimumab	Overall response rate 64% (58% per BICR) Disease control rate 84% (78% per BICR) Median PFS not reached 15-month PFS rate 75% Median OS not reached 15-month OS rate 84%
KEYNOTE 177 [28]	Metastatic previously untreated MSI-H CRC	Pembrolizumab vs. standard chemotherapy	Median PFS 16.5 vs. 8.2 months (HR 0.60; 95% CI 0.45–0.80; *p* = 0.0002) Estimated restricted mean survival after 24 months of follow-up 13.7 (range 12.0–15.4) vs. 10.8 months (range 9.4–12.2)

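### The safety endpoint counts adverse events through follow-up, but the follow-up schedules leave their assessment to discretion

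*Protocol article*

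**What the plan says.** Protocol article, section 2.3, lists as a secondary endpoint for both cohorts "the safety of the neoadjuvant combination immunotherapy, defined as the incidence of AEs during the treatment and follow-up phases", graded by CTCAE v5.0. The definition names two periods and gives them equal standing.

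The schedules under the Monitoring heading of each table read as follows:

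- **Table 1** (treatment and restaging, both cohorts): "AE/SAE assessment" at all visits.
- **Table 2** (surgical path): the AE/SAE row is marked at the surgery visit only. In follow-up there is a separate row, "AE assessment", with the entry "as clinically indicated".
- **Table 3** (non-operative management, NOM): a single row, "AE assessment", with the same discretionary entry.

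On quality of life, section 2.3 fixes the instruments and the period together: "EORTC QLQ-C30, EORTC QLQ-STO22 and EuroQol EQ-5D, during pre-operative treatment phase". Table 1 schedules the questionnaires to match, the last at restaging, and Tables 2 and 3 have none. Section 3 (Discussion) gives as one reason for studying NOM the morbidity of gastrectomy and "its potentially negative impact on long-term outcomes in terms of quality of life".

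**The concern.** An incidence needs a numerator collected in the same way throughout the period it covers. During treatment the plan asks about events at each visit. In follow-up it asks only when the investigator sees a reason to. An event that nobody asks about and no test reveals goes uncounted, so the reported incidence tends downwards, and events arising late after the last dose are the most exposed.

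The endpoint also has a use within the trial. Section 2.1 opens Cohort 2 only after Cohort 1 has been evaluated on all endpoints. With 18 and 13 patients, one or two unrecorded cases change a reported percentage visibly.

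**Working it through.** The plan gives no figure for this point, so there is none to reproduce. The check sets the endpoint against the schedules and dates the last mandatory assessment.

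**Inputs.** Last durvalumab dose: day 57 (section 2.5, Table 1). Restaging: weeks 12–14, printed as days 85–99 (Table 1). Surgery: weeks 15–18 (section 2.5, Table 2). Phase 1 follow-up: every 12 weeks for 2 years (Tables 2 and 3).

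**Week-to-day rule.** Table 1 equates weeks 12–14 with days 85–99. Since 12 × 7 + 1 = 85 and 14 × 7 + 1 = 99, week n is day 7n + 1.

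**Last mandatory AE/SAE assessment, NOM path (restaging).** 85 − 57 = 28 and 99 − 57 = 42, so 28–42 days after the last dose.

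**Last mandatory AE/SAE assessment, surgical path (surgery visit).** Week 15 is day 15 × 7 + 1 = 106 and week 18 is day 18 × 7 + 1 = 127. Then 106 − 57 = 49 and 127 − 57 = 70, so about 49–70 days after the last dose.

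**Visits after that.** 104 / 12 = 8.7, so roughly eight Phase 1 visits. None carries a mandatory adverse-event assessment on either path.

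**Side by side.** The endpoint covers treatment and follow-up. Systematic collection stops at restaging or at surgery. For the two years of protocol-scheduled follow-up, the endpoint has only discretionary data behind it.

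**Illustration only.** The documents give neither the true incidence of follow-up events nor the share that discretionary assessment would record, so both are assumed here. Let p be the true proportion of patients with a given event in follow-up and s the share of them recorded. The observed incidence is s × p, and the chance of recording at least one case among 13 patients is 1 − (1 − s × p)^13. With p = 20%:

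| s | Observed incidence | Chance of at least one recorded case in 13 |
|---|---|---|
| 1.0 | 20% | 94.5% |
| 0.8 | 16% | 89.6% |
| 0.6 | 12% | 81.0% |
| 0.5 | 10% | 74.6% |

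This shows the direction and how the loss scales. It does not estimate the loss in this trial.

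**The case against.** The strongest reply is that follow-up is not unmonitored. At Phase 1 visits both paths have a full physical examination, vital signs, chemistry, haematology, thyroid function and performance status, and concomitant medications are recorded at all visits. Operated patients also have a row for managing post-surgical complications. Many late immune-related events would surface this way. That stands, and it is why the understatement cannot be called large. It does not close the gap: events without a laboratory or examination sign still depend on someone asking, and the printed rule leaves that to judgement.

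Three stronger readings are tempting, and the documents do not support them.

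- *Serious events go uncollected under NOM.* Table 3 has no separate SAE row, but the follow-up columns of Table 2 have no SAE entry either. Seriousness is an attribute of an adverse event, so an adverse-event row does not exclude it. Reporting rules for serious events may stand in the full protocol, which is not shown.
- *NOM and operated patients are assessed differently, so a comparison is biased.* The follow-up rule is the same on both paths. The one additional assessment belongs to the surgery visit, which NOM patients do not have, and gastrectomy morbidity and mortality is an endpoint of its own. The article states no comparison of adverse-event incidence between the paths.
- *The absence of questionnaires in follow-up contradicts the plan.* It does not. Section 2.3 limits the quality-of-life endpoint to the pre-operative phase and Table 1 follows it. The Discussion explains why NOM is worth studying; it sets no quality-of-life objective for NOM.

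**Conclusion.** The mismatch over adverse events holds. The endpoint extends to follow-up, while Tables 2 and 3 state a discretionary rule there. This is a rule that the article prints, not a detail left to a fuller document: its schedules distinguish fixed entries, all-visit entries and discretionary ones. Systematic assessment ends 28–42 days after the last dose under NOM and about 49–70 days after it on the surgical path, with roughly eight scheduled visits still to come. Incidence over follow-up is likely understated, by an amount that the documents do not allow to be computed. The conclusion assumes that the printed tables govern data collection and that scheduled examinations and tests catch some events but not all.

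The quality-of-life matter is a limitation by choice. The long-term quality-of-life rationale in the Discussion is not evaluated by this trial, and no correction is required on that account.

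**What to change.** In Tables 2 and 3, replace the discretionary follow-up entry by a mandatory AE/SAE assessment (CTCAE v5.0) at every 12-weekly Phase 1 visit, identical on both paths. This needs no new visit or procedure; the cost is extra case report form pages at visits already scheduled. Section 2.1 already foresees amendments to study procedures before Cohort 2 opens.

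Alternatively, keep the tables and restrict the endpoint in section 2.3 to the period in which events are collected systematically. That period ends at restaging under NOM and at the surgery visit for operated patients, so the text should name its end. The cost is that the trial then makes no incidence statement about later events.

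Optional: repeat the existing questionnaires at the Phase 1 visits and amend the period in section 2.3 to match. This would describe quality of life after surgery and during NOM, at a small burden to patients and sites. Without a randomised comparator, and with NOM given only to complete responders, it could not show that avoiding gastrectomy preserved quality of life. If the questionnaires are not added, one sentence saying that the long-term rationale is not evaluated would suffice.
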